##### Social Support during School Sport

Social support received during school sport was measured using a modified version of an existing scale [26]. The scale included five items relating to students' beliefs about the instruction and social support students received from teachers and instructors during school sport. Students responded to a 5-point Likert scale (1 = Strongly Disagree to 5 = Strongly Agree). 'During school sport my teacher/instructor...' was the common stem and included the following items: i) appears enthusiastic about school sport, ii) teaches me valuable movement skills, iii) participates in physical activity or sport with me, iv) makes the activity enjoyable, v) encourages me to participate in the activity and vi) demonstrates sound knowledge and understanding of the activity. The internal consistency (α = 0.82) and test-retest reliability (ICC = 91, 95% CI = 0.85, 0.94) values were acceptable. The model fit indices for scale in the study population were good χ^2 ^= 31, *p *< 0.001, CFI = 0.99 and RMSEA = 0.05

##### Behavioural Strategies to Increase Physical Activity

Behavioural Strategies used to increase physical activity were measured using an adapted version of a scale derived from self-management theory for use with college students [27]. Participants were asked how often they used various strategies to increase their motivation for physical activities e.g. "I do things to make physical activity more enjoyable", and "I set goals to do physical activities". The modified seven-item instrument used a 5-point Likert scale ranging from 1 (never) to 5 (very often) for responses. Test-retest reliability of the modified version were ICC = 0.93 (95% CI = 0.89 to 0.96) whilst internal consistency was α = 0.78. The model fit indices for physical activity behavioural strategies in the study population were χ^2 ^= 263, *p *< 0.001, CFI = 0.92 and RMSEA = 0.12.

##### School Physical Activity Environment

Participants were asked to rate the quality, accessibility and availability of the physical activity facilities at their school using a scale developed for the current study. An example of an item was "The physical activity facilities at my school are easily accessible to me". Options ranged from 1 (Strongly disagree) to 5 (Strongly agree). The test-retest reliability (ICC = 0.69, 95% CI = 0.51 to 0.81), internal consistency (α = 0.80) and model fit indices (χ^2 ^= 98, *p *< 0.001, CFI = 0.96 and RMSEA = 0.07) were adequate.

##### Children's Physical Self-Perception Profile including the Perceived Importance Profile

The participants' physical self-perceptions were examined using the Children's Physical Self-Perception Profile (C-PSPP) inventory [28]. The C-PSPP is a 30-item questionnaire which consists of five equally divided sub-domains: perceived sport competence, physical conditioning, body attractiveness, physical strength, and physical self-worth. Each item presents two alternative statements, from which the participants can select which one best represents themselves using "sort of true" or "really true". The factor validity of the PSPP has been supported across various age groups, including adolescents [29,30]. Test-retest reliabilities and internal consistencies for all sub-domains were > 0.80. The model fit indices for the different sub-domains of the C-PSPP were considered acceptable to good in the study population. The Perceived Importance Profile (PIP) is integrated into the PSPP and centres on the importance the participants attach to four of the PSPP sub-domains, physical self-worth is excluding. The PIP utilises the same scoring structure as the PSPP and incorporates two items to measure the importance of each of the four sub-domains. The internal consistency (α = 0.78) and test-retest reliability (ICC = 91, 95% CI = 0.86, 0.94) values for the PIP were acceptable. The model fit indices for the PIP scale in the study population were χ^2 ^= 216, *p *< 0.001, CFI = 0.90 and RMSEA = 0.09.

### Process evaluation

In a study such as *Girls in Sport*, where each school will implement an intervention that is slightly different in its context, it is important to thoroughly document what is implemented, and the social context in which this occurs, as level of implementation can directly influence the outcomes of the study. In *Girls in Sport*, each school was required to submit an action plan for 2009 and 2010. This action plan formed part of the overall school plan for the year. School plans provide a framework to drive change within a school over a 3-year period in areas such as student engagement and retention, teacher quality, and connected learning [31].

The action plan for this study took each of the overarching outcomes and asked schools to write down specific strategies they would undertake to achieve this target and how they would measure success in achieving it, along with who would be involved. The activities also needed to demonstrate the area of the Health Promoting Schools Framework they represented.

Each school's specific action plan was then reviewed by the research team and Department of Education and Training staff. Schools participated in monthly teleconferences with their research partner to share their progress towards the study outcomes, specifically, the implementation of their strategies and any barriers they were experiencing. Possible solutions were brainstormed and, if further assistance was required, the problems were revised at the teleconference held every three weeks between the research team and Department staff and possible solutions fed-back to the school.

At the end of each year, schools were asked to document their progress towards the study outcomes based on their implementation of their specific strategies. They also evaluated any barriers to implementation. Interviews were also conducted at the end of the intervention with each school committee, other staff, executive, girls and boys, to triangulate these data and assess the extent to which the strategies were implemented. Observations of school sport and lunchtime activities will also take place.

### Sample size justification

The primary analysis in this study will be conducted in SAS using a linear mixed model. The test of interest will be an F test with a 1 degree of freedom contrast therefore it is computationally convenient to use the t test to perform the sample size calculations. Murray [32] proposed a method of sample size estimation and published relevant intraclass correlations on which to base the estimate. In lieu of a reliable estimate of the intra class correlation for the primary outcome measure of activity CPM an estimate of 0.01 was used in the a priori calculations. Effect sizes and variance estimates, 77.51SD(102.92) cpm, which was 18.4% of the baseline mean, were obtained from a previous study [33]. Based on these figures, a model based on a critical t value of 2.228 (taking into consideration the matching of the schools) is obtained for estimates based on 12 schools per group. Variance estimates are adjusted for clustering as proposed in Murray [32]; in brief the standard error of the estimate in the usual t estimation is replaced by $\sqrt{\frac{2\left({\hat{\sigma }}_{m}^{2}+m{\hat{\sigma }}_{g}^{2}\right)}{mg}}$ where ${\hat{\sigma }}_{m}^{2}$ is the estimate of the unadjusted subject component of the variance, ${\hat{\sigma }}_{g}^{2}$ is the unadjusted school component of the variance, m is the number of subjects per school and g is the number of schools per intervention. Sample sizes as low as 10 participants per school completing the study provided adequate power (>80% power and P < 0.05). Given that the estimate of effect could be considered optimistic for the present design a more modest effect size (10% of baseline mean, 42.07 cpm) was also considered. It was also anticipated that group sizes would vary between schools and therefore the estimates were based on a harmonic mean of 30 participants per school completing [34]. With this conservative mean effect size and a harmonic mean sample size of 30 completing the study the power remains high (0.987).

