#### Primary Outcome Measure

Objectively measured moderate-to-vigorous intensity physical activity was the primary outcome for the study. All participants wore an Actigraph accelerometer (7164 and GT1M models; Fort Walton Beach, FL) for seven consecutive days. This was attached to an adjustable elastic belt and worn over the right hip. Data were collected in 30-second epochs. The average number of minutes that the accelerometer was worn and the number of activity counts per minute (CPM) were calculated. Mean CPM as a summary measure of total physical activity in children has been validated against doubly labelled water [20]. Thirty-second activity counts were uploaded to determine the amount of time spent in light (LPA; 1.5-2.9 METs) moderate (MPA; 4-6.9 METs) and vigorous (VPA; ≥7 METs) physical activity during the monitoring period. Age-specific count ranges relating to the above intensity levels were based on prediction equations for energy expenditure [21]. Values were calculated for percentage of monitored time spent in light, moderate, and vigorous physical activity to account for variation in time spent wearing monitors. Participant data were included in analyses if accelerometers were worn for ≥600 minutes on ≥3 days [3].

All participants were asked to keep activity monitoring logs for the seven-day period when the accelerometers were being worn. Participants also received two text messages during the seven-day period. These text messages reminded the participants to keep wearing the accelerometers and to return them at the end of the seven-day period.

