### Statistical Analyses

#### Primary analyses

Statistical analysis of the primary outcome variable, percentage of time spent in MVPA, will be performed using a linear mixed model (PROC MIXED) is SAS. This model accounts for the hierarchical structure of the data. This is a standard statistical procedure for analysis of clustered datasets and the use of this methodology in school-based trials has been extensively documented by Murray [32]. Analysis of sedentary behaviour, light, moderate and vigorous activity will be performed in a similar manner. An advantage of the linear mixed model is that it incorporates all available data allowing for the analysis of partial datasets created when a participant drops out of the study or misses a study visit. Imputation of missing data will also be considered if missing data is substantial. This imputation will be performed using PROC MI and MIANALYSE. Sensitivity analyses will be performed. Mixed models will also be used to analyse all continuous secondary outcome variables.

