**Figure 1 F1:**
[figure not shown]
**Flow of schools and participants through the trial**.

**Table 2 T2:** Baseline demographic characteristics and outcome measures of *Girls in Sport *participants

	Intervention Group(1)	Control Group(0)	P	All
Age in years, mean (SE)	13.71 ± 0.04	13.48 ± 0.02	0.3512	13.60 ± 0.02
Physical activity* (n = 1199)				
Counts per minute, mean (SE)	428.40 ± 5.50	418.44 ± 5.22	0.2367	423.14 ± 3.79
Percentage time sedentary intensity	60.07 ± 0.32	61.22 ± 0.28	0.1210	60.83 ± 0.21
Percentage time light intensity	34.95 ± 0.27	33.95 ± 0.24	0.0655	34.26 ± 0.19
Percentage time moderate intensity	4.51 ± 0.08	4.32 ± 0.08	0.1482	4.38 ± 0.06
Percentage time vigorous intensity	0.455 ± 0.02	0.512 ± 0.02	0.6826	0.476 ± 0.01
Percentage time moderate-to-vigorous activity	4.97 ± 0.09	4.83 ± 0.09	0.3184	4.86 ± 0.06
Percentage of participants meeting recommended 60 mins of MVPA every day	1.9	1.1	0.253	1.5
Percentage of participants meeting recommended 60 mins of MVPA per day on average	10.6	9.6	0.682	10.1
Physical self-worth (n = 1467)	16.04 ± 0.14	16.40 ± 0.14	0.1798	16.22 ± 0.10
Sports competence (n = 1465)	15.42 ± 0.14	15.70 ± 0.13	0.2739	15.56 ± 0.10
Physical condition (n = 1468)	16.04 ± 0.14	16.38 ± 0.14	0.1389	16.21 ± 0.10
Body attractiveness (n = 1462)	14.02 ± 0.14	14.39 ± 0.15	0.2748	14.21 ± 0.10
Physical strength (n = 1461)	15.09 ± 0.13	15.35 ± 0.12	0.2002	15.22 ± 0.09
Physical activity confidence (n = 1510)	29.74 ± 0.16	29.88 ± 0.17	0.4675	29.81 ± 0.12
Enjoyment of physical activity (n = 1503)	29.77 ± 0.16	29.63 ± 0.16	0.5504	29.70 ± 0.12
Enjoyment of school sport (n = 1510)	28.06 ± 0.19	27.40 ± 0.20	0.0641	27.74 ± 0.14
Social support for physical activity (n = 1510)	12.54 ± 0.10	12.02 ± 0.11	0.0768	12.29 ± 0.08
Social support during school sport (n = 1503)	23.83 ± 0.16	23.65 ± 0.16	0.6594	23.75 ± 0.11
Strategies to increase physical activity (n = 1509)	25.32 ± 0.18	24.93 ± 0.19	0.3935	25.13 ± 0.13
School physical activity environment (n = 1508)	26.26 ± 0.16	25.88 ± 0.16	0.6952	26.07 ± 0.11
Perceived importance of physical activity (n = 1459)	22.42 ± 0.15	22.39 ± 0.15	0.8685	22.41 ± 0.11

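### The stated power of 0.987 is for counts per minute, not for percentage of time in MVPA, the primary outcome analysed; no power is stated for that outcome.

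*Protocol article*

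**What the plan says.** The Sample size justification names CPM as the primary outcome and takes its inputs from it. On the ICC: "In lieu of a reliable estimate of the intra class correlation for the primary outcome measure of activity CPM an estimate of 0.01 was used". On effect and variability: "Effect sizes and variance estimates, 77.51SD(102.92) cpm, which was 18.4% of the baseline mean, were obtained from a previous study". A smaller effect follows: "a more modest effect size (10% of baseline mean, 42.07 cpm) was also considered". The conclusion reads: "With this conservative mean effect size and a harmonic mean sample size of 30 completing the study the power remains high (0.987"). The same section uses more than 80% power as its standard of adequacy.

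Other sections name a different outcome. Table 1 gives prevention of a decline in MVPA as the primary outcome. Primary Outcome Measure says: "Objectively measured moderate-to-vigorous intensity physical activity was the primary outcome for the study". Primary analyses says: "Statistical analysis of the primary outcome variable, percentage of time spent in MVPA, will be performed using a linear mixed model".

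No effect size, standard deviation (SD), ICC or power is given for MVPA. Table 2 does report a baseline mean and standard error (SE) for "Percentage time moderate-to-vigorous activity".

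**The concern.** Two sections name different primary outcomes, and the only power figures belong to the one that the primary analysis does not test. This is more than a matter of labels, because power for a given relative effect depends on how variable the outcome is relative to its mean. The planning SD for CPM is 24% of its mean (102.92/420.7). The baseline SD of percentage of time in MVPA appears to be about 43% of its mean. A 10% difference is then 0.41 SD for CPM (42.07/102.92) but about 0.23 SD for MVPA (0.486/2.08).

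The interpretation of the result is at stake. A reader who sees a null result for MVPA beside a stated power of 0.987 could take it as strong evidence against a 10% effect. The plan contains no calculation that supports that reading.

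**Working it through.** **Method.** The formula is the one in the Sample size justification, with total variance split by the ICC:

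SE = SD × √{2[(1 − ICC) + m × ICC]/(m × g)}; power = P(T₁₀ < δ/SE − 2.228), where T₁₀ is Student's t with 10 degrees of freedom.

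From the plan: g = 12 schools per group, m = 30 completing per school, ICC = 0.01, critical t = 2.228 (the two-sided 5% value on 10 degrees of freedom).

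**Step 1: reproduce the stated figure (CPM).** SD = 102.92, δ = 42.07.

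- SE = 102.92 × √[2(0.99 + 0.30)/360] = 8.713
- δ/SE = 4.829
- Power = 0.987 (0.9868), as stated.

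**Step 2: inputs for MVPA.** The plan states none, so these are assumptions.

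- SD: Table 2 gives mean 4.86 and SE 0.06 with n = 1199. Treating the SE as SD/√n, SD = 0.06 × √1199 = 2.08 percentage points. An SE that rounds to 0.06 lies between 0.055 and 0.065, so the SD lies between 1.90 and 2.25.
- Effect: the 10% carried over from CPM, 0.10 × 4.86 = 0.486 points.
- ICC: 0.01, also carried over from CPM.

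**Step 3: same method, MVPA.**

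- SE = 2.078 × √[2(0.99 + 0.30)/360] = 0.176
- δ/SE = 2.763
- Power = 0.70 (0.78 at SD 1.90, 0.62 at SD 2.25).

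Table 2's arm-level SEs of 0.09, with about 600 girls per arm assumed, imply an SD of 2.20 and power of 0.64. With 11 degrees of freedom, as in the note to Table 2, power is 0.71.

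**Step 4: sensitivity (SD 2.08; 10% effect unless stated).**

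| Scenario | ICC 0.01 | ICC 0.03 | ICC 0.05 |
|---|---|---|---|
| 30 per school | 0.70 | 0.53 | 0.41 |
| 50 per school (1199/24 ≈ 50 usable at baseline) | 0.85 | 0.63 | 0.48 |
| 30 per school, baseline-adjusted, assumed correlation 0.4 to 0.6 | 0.78–0.88 | 0.61–0.73 | 0.48–0.61 |
| 30 per school, 18.4% effect (0.894 points) | 0.99 | 0.96 | 0.91 |

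The baseline-adjusted row multiplies the SD by √(1 − ρ²) and leaves the ICC unchanged.

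**Step 5: detectable difference.** For 80% power, δ = (2.228 + 0.879) × SE, where 0.879 is the 80th percentile of t on 10 degrees of freedom. With 30 per school this is 3.107 × 0.1759 = 0.55 points (11% of the mean) at ICC 0.01, 0.66 points (14%) at ICC 0.03 and 0.75 points (15%) at ICC 0.05.

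**The case against.** The strongest objection is to the 0.70, not to the mismatch. The 0.70 does not rest wholly on the plan's own inputs: only the formula, g, m and critical t carry over without a change of outcome. The SD is back-calculated from an SE rounded to two decimals, and the note to Table 2 does not make clear whether the SEs are raw or model-adjusted. The ICC and the 10% effect were stated for CPM, and nothing says that a 10% difference in CPM corresponds to a 10% difference in MVPA. At 12% the same calculation gives 0.85, at 15% 0.96, and at the plan's other relative effect, 18.4%, 0.99. All of this stands, so 0.70 is an illustration.

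The comparison of relative variability is also imperfect. It sets a baseline SD from this sample against an SD from a cited study that is not shown, which could be an SD of change or a residual SD. On the Table 2 basis, CPM has an SD of 3.79 × √1199 ≈ 131, or 31% of its mean of 423.14, so the gap from 43% is narrower. If the MVPA SD is scaled by 102.92/131.2 (an assumption), power is 0.89 at ICC 0.01, 0.75 at 0.03 and 0.63 at 0.05. For the same reason, a reader who infers that the CPM planning SD was too small goes further than the documents allow.

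Nor is m = 30 established: baseline gave about 50 usable records per school, though before 18 months of attrition. The plan also says openly that it had no reliable ICC.

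None of this removes the contradiction over which outcome is primary, or supplies a power figure for MVPA.

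**Conclusion.** The concern holds as an internal inconsistency. The arithmetic behind 0.987 is correct, but it is for CPM and does not apply to the primary test of a 10% effect on percentage of time in MVPA. No power is stated for that test.

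Under the carried-over assumptions (SD 2.08, 10% effect, ICC 0.01, 30 per school), power is about 0.70, short of the plan's criterion of more than 80%. Larger ICCs lower it. More girls per school, baseline adjustment or a larger effect raise it, to 0.85 or more in some cases. For a 10% effect, none of the cases examined reaches 0.987.

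A reader might infer that the trial is underpowered. The documents do not support that: the answer depends on an MVPA effect, SD, ICC and follow-up numbers that the plan does not state.

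**What to change.** In the Sample size justification:

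- Name percentage of time in MVPA as the primary outcome, consistent with Table 1, Primary Outcome Measure and Primary analyses.
- Replace 0.987 with power for that outcome, or with a detectable difference (about 0.55 points, 11% of the mean, at 80% power, ICC 0.01 and 30 per school), shown over ICC 0.01 to 0.05. State the SD, the effect and any baseline adjustment assumed.
- Keep the existing calculation if wanted, labelled as applying to CPM and not to the primary outcome. It should not be called a secondary-outcome calculation unless CPM is first listed as one, which neither Table 1 nor the Statistical Analyses section does.

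This rewrites one paragraph and needs no extra schools or girls. The only cost is a less favourable stated power.

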### Statistical Analyses

#### Primary analyses

Statistical analysis of the primary outcome variable, percentage of time spent in MVPA, will be performed using a linear mixed model (PROC MIXED) is SAS. This model accounts for the hierarchical structure of the data. This is a standard statistical procedure for analysis of clustered datasets and the use of this methodology in school-based trials has been extensively documented by Murray [32]. Analysis of sedentary behaviour, light, moderate and vigorous activity will be performed in a similar manner. An advantage of the linear mixed model is that it incorporates all available data allowing for the analysis of partial datasets created when a participant drops out of the study or misses a study visit. Imputation of missing data will also be considered if missing data is substantial. This imputation will be performed using PROC MI and MIANALYSE. Sensitivity analyses will be performed. Mixed models will also be used to analyse all continuous secondary outcome variables.

#### Secondary analyses

Model Testing, Mediation and Moderation Analyses.

Two types of analyses will be conducted to explore the theoretical assumptions of the intervention. First, Social Cognitive Theory will be tested in AMOS using structural equation modelling. Hypothesized mediators of physical activity behaviour change will be examined using multilevel linear analysis and a product-of-coefficients test that is appropriate for cluster randomized controlled trials [35]. Potential moderators of the intervention effects (e.g. ethnicity, socio-economic status and type of school) will also be explored using multi-level modelling. The baseline analyses presented in the current paper are conducted using PROC MIXED (SAS V 9.0, SAS Institute, Cary NC) to adjust for the matched and clustered nature of the dataset [32].

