### Randomization and study design

This was a group randomized controlled trial with school as the unit of randomization. Each matched pair of schools was randomly allocated to the intervention or control group using a computer-based random number producing algorithm. This was undertaken by a researcher independent of the project and then communicated to the research team who informed each school of its allocation. Due to the timeframe of the study, formative research was required to be conducted in the intervention schools in Term 4 (October to December 2008). This meant randomization needed to occur prior to baseline data collection.

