#### Potential mediators and moderators of physical activity behaviour change

The questionnaires used to measure potential mediators and moderators were administered in a secluded area on two separate days to increase the accuracy of responses and reduce participant burden. The first visit was when the accelerometers were distributed and the second when the accelerometers were collected approximately seven days later. On the first visit the enjoyment of physical activity and school sport, self-efficacy in physical activity, social support for physical activity, social support during school sport, strategies to increase physical activity, and school physical activity environment scales were administered. On the second visit, the physical self-concept and perceived importance of physical activity scales were administered.

Potential mediators assessed included enjoyment of physical activity and school sport, physical activity self-efficacy, social support for physical activity, social support during school sport, strategies to increase physical activity, school physical activity environment, physical self-concept and perceived importance of physical activity. We conducted our own validity and reliability of all scales. To do this, four schools were selected at random to complete the scales, approximately one week apart: Seventy-five students from two schools completed those administered on the first visit, and another 75 from the other two schools completed those administered on the second visit. Intra-class correlations were performed to assess test-retest reliability and Cronbach alphas were used to assess internal consistency. AMOS 17.0 (Small Waters Corp., Chicago IL) was used to assess the construct validity of the different measures using the baseline data. Model fit was assessed using multiple indices, including chi-square index, comparative fit index (CFI) and root mean square of approximation (RMSEA).

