## Results

A total of 32 schools from four geographical regions in New South Wales tendered an Expression of Interest for the study to the NSW Department of Education and Training and were assessed for eligibility. The four regions, outer Sydney metropolitan, Illawarra and South Coast, Hunter and New England, and the North Coast incorporated a range of socio-economic, urban and rural settings. From the original 32 schools, 8 were unable to be matched based on the *a priori *criteria, leaving 24 that were matched and randomly allocated to the intervention or control group. One of the schools withdrew after being allocated to the control group and was replaced with another school that was nominated by the NSW Department of Education and Training as a suitable school to be matched to the intervention school. The flow of schools and individual students through the enrolment and allocation stages of the study are displayed in Figure 1. Eighty-six percent of eligible girls completed baseline assessments, 771 in the intervention group and 747 in the control group. Table 2 shows the baseline characteristics of participants on demographic, outcome and mediator/moderator variables.

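### The structural equation model of the theory is specified in AMOS with no provision for school clustering, unlike the companion analyses; the effect is modest and confined to a secondary analysis

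*Protocol article*

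**What the plan says.** The design section of the protocol article states: "This was a group randomized controlled trial with school as the unit of randomization". The Results describe eight schools that could not be matched, "leaving 24 that were matched and randomly allocated to the intervention or control group".

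Under Secondary analyses, the theory test has one sentence: "Social Cognitive Theory will be tested in AMOS using structural equation modelling". It does not mention schools. The next sentences do. On mediators the article says, in part: "Hypothesized mediators of physical activity behaviour change will be examined using multilevel linear analysis and a product-of-coefficients test that is appropriate for cluster randomized controlled". Moderators "will also be explored using multi-level modelling". The same paragraph has the baseline comparisons fitted in PROC MIXED to allow for matching and clustering. Under Primary analyses, the main outcome is analysed with a linear mixed model chosen because it respects the hierarchy, and continuous secondary outcomes are treated likewise.

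AMOS also appears in the section on potential mediators and moderators, where it "was used to assess the construct validity of the different measures using the baseline data". Clustering is not mentioned there either.

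**The concern.** Girls in one school share facilities, teachers and a sport programme. Two of the scales ask about exactly these things: the environment scale rates the school's own facilities, and the school-sport support scale rates the teacher or instructor. Responses to such items are correlated within schools.

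A structural equation model (SEM) that treats about 1,500 girls as independent has two problems:

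- Standard errors are too small for paths between variables that both cluster by school, so some theory links would be declared supported too readily.
- The pooled covariance matrix mixes within-school and between-school associations. For the environment scale, the path coefficient then has no single meaning. This does not depend on any design-effect figure.

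The SEM and the multilevel mediation analysis would use overlapping variables from the same girls. If only one of them allows for schools, they could disagree for that reason alone.

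**Working it through.** **The plan's own figures.** The article prints no design effect or intraclass correlation (ICC) for the SEM constructs, so there is nothing of its own to reproduce here. Its one power figure, 0.987 for the primary outcome, does reproduce. SE = √(2 × 102.92² × (0.99 + 30 × 0.01)/(30 × 12)) = 8.713; 42.07/8.713 − 2.228 = 2.60, and the t distribution on 10 df gives 0.987. That figure does not bear on the SEM.

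**Step 1: design effect for a group mean difference.** Inputs are the means, SEs and P values in Table 2 and the 11 df in its note. Implied SE = |difference| / t₁₁(P). Naive SE = √(SE₁² + SE₂²). Design effect = (implied SE / naive SE)². This assumes that the printed SEs ignore clustering and that the printed difference is the one tested. ICC = (design effect − 1)/(m − 1), with m = n/24.

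| Scale | Difference | P | t₁₁ | Implied SE | Naive SE | Design effect (rounding range) | m | ICC |
|---|---|---|---|---|---|---|---|---|
| School environment | 0.38 | 0.6952 | 0.402 | 0.945 | 0.226 | 17.4 (15.5–19.6) | 62.8 | 0.27 |
| Social support for activity | 0.52 | 0.0768 | 1.952 | 0.266 | 0.149 | 3.2 (2.8–3.7) | 62.9 | 0.036 |
| Support during school sport | 0.18 | 0.6594 | 0.453 | 0.397 | 0.226 | 3.1 (2.6–3.7) | 62.6 | 0.034 |
| Strategies | 0.39 | 0.3935 | 0.888 | 0.439 | 0.262 | 2.8 (2.5–3.1) | 62.9 | 0.029 |
| MVPA | 0.14 | 0.3184 | 1.045 | 0.134 | 0.127 | 1.1 (0.9–1.4) | 50.0 | 0.002 |

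The other nine questionnaire scales give: body attractiveness 2.5, sports competence 1.6, physical self-worth 1.6, enjoyment of school sport 1.35, physical condition 1.2, strength 1.2, enjoyment of activity 1.0, perceived importance 0.7 and physical activity confidence (self-efficacy) 0.6.

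Each estimate rests on 11 df. The 95% limits are the estimate times 11/21.9 = 0.5 to 11/3.8 = 2.9.

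**Step 2: what this means for paths between girl-level variables.** For such a path the approximate design effect is 1 + (m − 1) × ICC_x × ICC_y. The true error of a nominal 5% test is 2 × (1 − Φ(1.96/√design effect)).

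- Environment with social support: 1 + 61.9 × 0.266 × 0.036 = 1.59; error 12%.
- Environment with school-sport support: 1 + 61.6 × 0.266 × 0.034 = 1.55; error about 12%.
- Environment with strategies: 1 + 61.9 × 0.266 × 0.029 = 1.48; error 11%.
- Environment to MVPA: 1 + 49 × 0.266 × 0.002 = 1.03; error stays near 5%. At the upper ends of the rounding ranges the design effect is about 1.1.
- Social support to MVPA: 1 + 49 × 0.036 × 0.002 = 1.00.

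**Step 3: paths from a school-level variable.** Here the Step 1 design effects apply directly. The same error formula gives 24% at 2.8, 27% at 3.2 and 64% at 17.4. These hold only if allocation or another school-level variable is in the model.

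**The case against.** The article gives the SEM one sentence, with no path diagram, time point or covariance input. It does not say single-level and does not say that clustering will be ignored. A condensed article may leave that to a fuller plan, and AMOS run on a pooled within-school covariance matrix is not excluded. This stands as a limit on wording: a reader might infer a decision to ignore schools, and the text shows only that no provision is stated. The omission is still worth raising, because the method and software are fixed and the neighbouring analyses each state their provision.

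A reader might also infer false-positive rates of up to 64%. The document does not support that. It gives the SEM the task of testing the theory, and sends mediation of behaviour change and moderation of the intervention effect to multilevel methods. Nothing places allocation in the SEM.

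Nor does Table 2 support strong clustering across the constructs. Four of 13 scales reach about 3, and only environment is well above that. The three values near 3 are the largest of the other 12 noisy estimates, and self-efficacy, a natural component of the theory, sits at about 0.6.

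Finally, the back-calculation is fragile. The note to Table 2 calls the values raw means and also adjusted least-squares estimates. The same method gives about 28 for age and 23 for percentage of vigorous time, which suggests that the printed difference is not always the one tested. That objection stands, so the figures are indicative only.

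**Conclusion.** The point holds in a limited form. The test of Social Cognitive Theory is specified without provision for schools, in contrast to the other analyses, and a better method is available at little cost.

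The expected inflation is about 1.5 to 1.6 for paths joining the environment scale to support or strategies (nominal 5% becomes about 11 to 12%). It is negligible for paths to MVPA. The mixing of within-school and between-school associations for the environment scale is a separate problem of interpretation.

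These sizes assume that the Table 2 SEs are unadjusted, that the printed differences are those tested, and that baseline clustering resembles clustering in the data the SEM will use. No size has been calculated for any effect on the model chi-square. The primary test and the mixed-model secondary outcomes are not affected.

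**What to change.** State in the plan how the SEM accounts for schools. Any one of these would do:

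- fit it with school as the cluster, using cluster-robust standard errors and a scaled chi-square;
- fit it as a two-level SEM;
- keep AMOS but analyse only the pooled within-school covariance matrix, and leave all inference on allocation and school-level variables to the multilevel analyses already planned.

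The cost is a change of software or options and some extra analysis time. With 24 schools, robust standard errors are themselves approximate, and the plan should say so. The construct-validity models have already been run and are not part of this change.
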